### Study design

This trial is a prospective, parallel two-armed randomized (1:1) controlled trial with a nested full economic evaluation with 6 months follow-up. The trial is expected to run from October 2021 to May 2022. Prior to randomization, participants must give written consent in accordance with the Helsinki declaration [44]. Data will be anonymized and stored in accordance with the Danish Data Protection Rules [45]. The trial has been approved by the Regional Ethical Committee for Medical Research in the North Denmark Region (no.: N-20200076) and the Danish Data Protection Agency. Any protocol modifications will only be implemented after approval from the Regional Ethical Committee.

The trial is single-blinded, as the participants are unaware of their group allocation. The specialized COPD community nurses will not be blinded, as they will know whether the COPD prediction algorithm supports them or not. Outcome assessment will not be blinded.

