### Recruitment

The recruitment takes place in Aalborg Municipality. Specialized COPD community nurses identify eligible participants prior to randomization (Fig. 2). Subsequently, researchers will contact the participants to give them further information about the trial, answer potential questions, and guide them regarding the written consent form. A written consent form and questionnaires will be sent to eligible participants after receiving oral consent. If the participants still wish to participate in the trial, they will return the questionnaires and the written consent form via mail using a second pre-stamped envelope. The researchers’ telephone numbers are stated on the questionnaires giving the participants the opportunity to receive help in answering the questionnaires.

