### Randomization

The participants will, by a computer-generated list be allocated randomly (1:1) across two treatment arms: an intervention group (telehealth with algorithm) or to a control group (telehealth without the algorithm). The allocation sequence will be concealed until the participants are enrolled and assigned to the two groups. The randomization will not be performed until the included participants have signed informed consent and completed baseline questionnaires. Researchers at Aalborg University will generate the allocation sequence, enroll the participants, and assign the participants to their respective groups.

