#### Explorative outcomes

To assess the participants’ health literacy level at baseline using the European Health Literacy Survey Questionnaire (HLS-EU-Q16) [51], supported by further assessment with the Danish Test of Functional Health Literacy in Adults (the Danish TOFHLA) [52] during the trial period to examine whether the effect of the COPD prediction algorithm is similar in patients with COPD, regardless of health literacy levelTo examine whether the specialized COPD community nurse’s estimate of the individual participant’s level of health literacy influences the effect of the COPD prediction algorithmTo evaluate the specialized COPD community nurses’ experiences with the usability of the COPD prediction algorithm using interviewsTo evaluate the participants’ experiences with the usability of the telehealth system after trial completion using the Danish Telehealth Usability Questionnaire (D-TUQ) questionnaire [53]To evaluate the participants’ experiences with data ethical aspects after trial completion using qualitative research interviews

The SF-12v2, the EQ-5D-5L, HLS-EU-Q16, and questions about demographic characteristics are sent to the participants by letter at baseline. The D-TUQ, SF-12v2, and EQ-5D-5L are sent at follow-up (Table 1). If a participant is unable to return the questionnaires by mail, a research assistant will pick up the letter at the participant’s address to promote complete follow-up.

**Table 1 Tab1:** An overview of the questionnaires that the participants receive at baseline, intermediate, and after 6 months follow-up

Name of the questionnaire	Time point for each outcome
The 12-item Short Form Health Survey (version 2)	Baseline, 6 months follow-up
The EuroQol 5-Dimension questionnaire	Baseline, 6 months follow-up
The European Health Literacy Survey Questionnaire	Baseline
Questions about demographic characteristics	Baseline
The Danish Test of Functional Health Literacy in Adults The	Intermediate
Danish Telehealth Usability Questionnaire	6 months follow-up

During the trial period, the level of health literacy will be assessed further with the Danish TOFHLA. Additionally, the COPD community nurses will be asked to provide an estimate of the individual level of health literacy among the participants with COPD [52].

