The HLS-EU-Q16 and the Danish TOFHLA provide an individual health literacy score. The HLS-EU-Q16 provides a score ranging from zero (inadequate) to 50 (excellent) and divides the participants into four (HL) groups on this basis. The Danish TOFHLA provides a score ranging from zero (inadequate) to 100 (adequate) and divides the participants into three (HL) groups on this basis. It will be examined whether the division into different groups is similar regardless of health literacy being assessed with the HLS-EU-Q16 or the Danish TOFHLA. One-Way ANOVA will be used to test pre (baseline)-post (follow-up) between-HL-group (as measured with the HLS-EU-Q16) differences in the number of exacerbations. One-Way ANOVA will also be used to test pre (baseline)–post (follow-up) between-HL-group (as measured with the Danish TOFHLA) differences in the number of exacerbations. Furthermore, the specialized COPD community nurses estimate an individual health literacy score among their COPD patients ranging from zero (inadequate) to 10 (adequate) based on their professional judgment. This individual health literacy score provided by the specialized COPD community nurses divides the participants into three (HL) groups. One-Way ANOVA will be used to test pre (baseline)–post (follow-up) between-HL-group differences in the number of exacerbations. It should be noted that the individual health literacy score provided by the specialized COPD community nurses will be compared to the scores obtained with both the HLS-EU-Q16 and the Danish TOFHLA to examine if their professional judgment with regards to health literacy is in line with the standardized scores provided by these tests.

Descriptive statistics will be conducted for the D-TUQ by examining the range, median, and frequency of responses for each item including plots. The questionnaire check marks are listed on a Likert scale ranging from one (disagree) to seven (agree) indicating each participants’ level of agreement with the questions.

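### Two of the three literacy measures used to judge effect modification come after randomisation (the nurse score by inference), and the unblinded nurse score can react to arm and outcome

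*Protocol article*

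**What the plan says.** Two of the explorative outcomes in the protocol article are effect-modification questions: whether the algorithm works equally well at all literacy levels, and whether the nurse's view of a participant's literacy influences the algorithm's effect. Three measures serve them.

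- **HLS-EU-Q16.** Table 1 places it at baseline. The Randomization section says "The randomization will not be performed until the included participants have signed informed consent and completed baseline questionnaires", so this measure precedes allocation.
- **Danish TOFHLA.** The text says "During the trial period, the level of health literacy will be assessed further with the Danish TOFHLA", and Table 1 lists it as intermediate. It therefore follows allocation.
- **Nurse estimate.** The sentence after the TOFHLA timing says "the COPD community nurses will be asked to provide an estimate of the individual level of health literacy among the participants with COPD". No date is given. Statistical methods describes a score "ranging from zero (inadequate) to 10 (adequate) based on their professional judgment", which is then cut into three groups.

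On blinding, Study design says "The specialized COPD community nurses will not be blinded"; participants are blinded. The only test given for the literacy questions is a one-way ANOVA of exacerbation counts between literacy groups, run once for each measure.

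**The concern.** An effect modifier should be fixed before treatment can act on it. A rating made during follow-up can depend on the arm and on what has already happened to the participant. The primary outcome counts all-cause acute hospitalisations from baseline, so an admission before the rating is already part of the outcome. The nurses are in continuing contact with participants (section on minimising loss to follow-up) and may know of such admissions. They know the arm, and the algorithm gives them additional alerts in one arm only. A subjective score could therefore move with admissions by a different amount in each arm.

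At stake is the answer to an explorative question with practical weight: a finding that the algorithm works only at some literacy levels could influence who is offered it.

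**Working it through.** **Plan's own figures.** The document gives no figure for the literacy analysis. The nearest is the sample size, which supplies simulation inputs: control mean 2, intervention mean 1, two-sided 0.05, 90% power, about 100 per arm. The stated 85 per arm reproduces when the printed 2 is taken as an SD: 2 × (1.960 + 1.282)² × 2² / 1² = 84.1, rounded up to 85, and 85 / (1 − 0.15) = 100. One simulation setting below therefore uses a control SD of 2.

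**Mechanism.** Let the recorded score be L* = L − b × E, where L is true literacy in SD units, E the number of admissions before the rating and b the drift per admission. Since E is part of the outcome count, b > 0 makes low L* go with high counts inside an arm even if L is irrelevant. The interaction is the difference between the arms' slopes on L*. Equal b gives similar slopes, which largely cancel. Unequal b leaves a false interaction.

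**Simulation A.** 200 patients, 1,500 runs per setting, control mean 1, rate ratio 0.7 at every literacy level, dispersion 1, no true modification. Poisson model with robust variance and an arm-by-low-literacy term; at most two early admissions count towards drift.

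| Drift (intervention, control) | Interaction ratio | False positives |
|---|---|---|
| Rated before randomisation | 1.00 | 5.7% |
| 0, 0 | 0.99 | 6.3% |
| 0.25, 0 | 1.25 | 10.5% |
| 0.5, 0 | 1.62 | 20.1% |
| 0.5, 0.25 | 1.21 | 9.2% |

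**Simulation B.** 200 participants, 1,000 runs per setting, control mean 2, rate ratio 1.0 or 0.5, Poisson counts or overdispersed counts (control SD 2), literacy unrelated or mildly prognostic (rate ratio exp(−0.2) per SD), no true modification, score taken at mid-trial.

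| Behaviour of the score | False interaction |
|---|---|
| Unaffected | 4–7% |
| Constant 0.5 SD shift in one arm | 5–7% |
| Equal drift in both arms, b = 0.1 to 0.5 | 5–9% |
| Drift differing by arm, b = 0.1 | 6–13% |
| Drift differing by arm, b = 0.25 | 13–34% |
| Drift differing by arm, b = 0.5 | 19–74% |

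The direction follows the arm. With overdispersed counts and b = 0.25, the false ratio per SD is 1.20 to 1.24 if only control scores drift and 0.81 to 0.86 if only intervention scores drift. With equal drift it is 1.00 to 1.05.

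**The ANOVA as printed.** Its single factor is literacy group, so it compares counts between groups and not the algorithm's effect between groups. In simulation B:

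- With a score unaffected by arm or outcome and literacy merely prognostic, it rejects in 37–80% of runs although no modification exists.
- With literacy unrelated to outcome and no drift, it rejects in 4–5%.
- With equal drift in both arms it rejects in 9–18% (b = 0.1), 35–63% (b = 0.25) and 88–99% (b = 0.5).
- One-arm drift can also distort it, but not always. At b = 0.25 and rate ratio 0.5, control-only drift gives 28% and 38% (Poisson, overdispersed), while intervention-only drift leaves about 5%.

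**The case against.** Four points on the other side carry weight.

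1. **The nurse rating is undated.** Table 1 covers only participant questionnaires, and nothing excludes an early rating. This stands: the timing is an inference from the sentence's position after the TOFHLA schedule. Equally, nothing requires the rating before allocation or blind to arm and admissions.
2. **Late measurement alone does little to an interaction test.** A constant arm shift or equal drift leaves error near nominal. The larger figures need drift that differs by arm, and the documents give no evidence of its size or form. This stands. A reader might take 10–20% as the expected error of the planned analysis; it is not, because the drift is assumed and the interaction model is not the printed test.
3. **The TOFHLA differs from the nurse score.** It is a scored test from participants who do not know their arm, so arm-dependent drift is weakly supported. What remains is missing scores after early death, illness or withdrawal, which the planned multiple imputation may only partly address.
4. **HLS-EU-Q16 is sound.** A reader might infer that the whole literacy question is irreparably biased. The documents do not support that: this measure precedes allocation and can carry the modification analysis. It cannot, however, replace the nurse estimate, which has an explorative outcome of its own.

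**Conclusion.** The point holds, mainly for the nurse score. A subjective rating, undated but most naturally read as made during the trial by nurses who know the arm and may know of admissions, is unsuitable for judging whether the algorithm's effect depends on literacy. The illustrative false interaction rate is about 10–20% at 0.25 to 0.5 SD drift in one arm under simulation A, and 13–34% and 19–74% under the protocol's own control mean. It is about 5–9% if drift is equal. All drift sizes are assumptions.

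The TOFHLA is a lesser case, exposed mostly through missing scores. The printed ANOVA cannot answer the modification question for any of the three measures, so correcting the timing alone is not enough. The reach is limited to explorative outcomes: the primary analysis and the HLS-EU-Q16 measurement are untouched.

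**What to change.** - **Nurse rating.** Collect it at the eligibility step and state that timing. The Recruitment section already says "Specialized COPD community nurses identify eligible participants prior to randomization", and the trial population already uses the telehealth system, so the rating needs no new contact with participants.
- **TOFHLA.** Leave it where it is and use it only for description and for the agreement comparison already planned in Statistical methods. Moving it to baseline would lengthen a mailed packet that must come back before randomisation, in a trial that expects recruitment to be hard.
- **Analysis.** Base the modification question on HLS-EU-Q16 and the pre-randomisation nurse rating, in the Poisson model: log(mean count) = β0 + β1·arm + β2·literacy + β3·arm × literacy. Report exp(β3) with its confidence interval in place of the one-way ANOVA.
- **Ratings already made after allocation.** Label these as descriptive and leave the modification analysis to HLS-EU-Q16.

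The cost is one nurse form moved earlier, a TOFHLA used descriptively, and one term added to a model the protocol already specifies for its primary outcome.

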### Statistical methods

Overall, the statistical methods will follow an intention-to-treat principle [54]. Results from the trial will be presented in accordance with the Consolidated Standards of Reporting Trials (CONSORT) for randomized trial guidelines [55] as well as the Consolidated Health Economic Evaluation Reporting Standards (CHEERS) [56]. Missing data will be subject to multiple imputation [57]. If there is a need for an adjustment of the participants’ baseline characteristics due to differences among the two groups, this will be performed.

To assess the primary outcome, Poisson regression with exponentiated coefficients will be used to produce incidence rate ratios. In assessing HRQoL, generalized linear models [58] will be used to model EQ-5D-5L and the two SF12v2 summary scores; the physical component score (PCS-12) and the mental component score (MCS-12). To assess the secondary outcome of cost-effectiveness, an ICER point estimate will be calculated after 6 months follow-up. The ICER is defined as the difference in the average costs between the two alternatives divided by the difference in average effectiveness between the same alternatives [59]. For the ICER calculation, the effectiveness for both alternatives is assessed based on the utility scores from the EQ-5D-5L questionnaire, with Danish societal weights that are unpublished but under journal peer review [50]. With the help of information on within-trial survival time, QALYs can then be elucidated with linear interpolation of utility scores between baseline and follow-up at six months as the area under this curve [59].

In assessing base-case total costs for both alternatives, this trial adopts a healthcare sector perspective, meaning that the following cost categories are included: additional costs in implementing the algorithm, in- and outpatient hospital costs, medication costs, costs from visiting primary care and general practitioners in particular, community care costs associated with home nurse visits, individual care, and practical help as well as rehabilitation activities in the municipalities. Treatment effects for effectiveness and costs will be calculated separately by applying generalized linear models [58] and will be reported both as an unadjusted estimate and as an estimate that controls for meaningful baseline differences. Finally, the economic evaluation will nuance base-case results by applying both one-way and probabilistic sensitivity analysis (PSA) to allow decision-makers to evaluate the impact of parameter uncertainty that might occur during the trial period on cost-effectiveness at a range of willingness-to-pay levels for an improvement in QALYs [60, 61].

The HLS-EU-Q16 and the Danish TOFHLA provide an individual health literacy score. The HLS-EU-Q16 provides a score ranging from zero (inadequate) to 50 (excellent) and divides the participants into four (HL) groups on this basis. The Danish TOFHLA provides a score ranging from zero (inadequate) to 100 (adequate) and divides the participants into three (HL) groups on this basis. It will be examined whether the division into different groups is similar regardless of health literacy being assessed with the HLS-EU-Q16 or the Danish TOFHLA. One-Way ANOVA will be used to test pre (baseline)-post (follow-up) between-HL-group (as measured with the HLS-EU-Q16) differences in the number of exacerbations. One-Way ANOVA will also be used to test pre (baseline)–post (follow-up) between-HL-group (as measured with the Danish TOFHLA) differences in the number of exacerbations. Furthermore, the specialized COPD community nurses estimate an individual health literacy score among their COPD patients ranging from zero (inadequate) to 10 (adequate) based on their professional judgment. This individual health literacy score provided by the specialized COPD community nurses divides the participants into three (HL) groups. One-Way ANOVA will be used to test pre (baseline)–post (follow-up) between-HL-group differences in the number of exacerbations. It should be noted that the individual health literacy score provided by the specialized COPD community nurses will be compared to the scores obtained with both the HLS-EU-Q16 and the Danish TOFHLA to examine if their professional judgment with regards to health literacy is in line with the standardized scores provided by these tests.

Descriptive statistics will be conducted for the D-TUQ by examining the range, median, and frequency of responses for each item including plots. The questionnaire check marks are listed on a Likert scale ranging from one (disagree) to seven (agree) indicating each participants’ level of agreement with the questions.

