#### Primary outcome

The primary outcome is the between-group difference in the number of observed exacerbations defined as an all-cause acute hospitalization from baseline to follow-up. The trial hypothesizes that integrating a COPD prediction algorithm into the telehealth system will lead to a significantly lower number of exacerbations through early identification and timely preventive treatment

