#### Secondary outcomes

The secondary outcomes include:
The change in health-related quality of life (HRQoL) using the 12-item Short Form Health Survey (version 2) (SF-12v2) [46] and the EuroQol-5 Dimension Questionnaire (EQ-5D-5L) [47] at the individual level from baseline to follow-up at 6 months. The trial hypothesizes that the difference in HRQoL from baseline to follow-up in both groups decrease since the participants have lived 6 months longer with COPD. However, it is expected that the decrease in HRQoL will be lower for the intervention group compared to the control group. Both questionnaires have previously been validated in the Danish population [48–50].The incremental cost-effectiveness ratio or ICER measured as the total cost per quality-adjusted life years (QALY) gained for the cost categories included in the study from baseline to follow-up at 6 months. It is hypothesized that the cost of hospital contacts will decrease, but it is unknown whether this cost is offset by an increase in other cost categories such as community care

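### Baseline adjustment is triggered by observed imbalance, with need undefined and no primary estimate named, so precision is given up and the main result is left open

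*Protocol article*

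**What the plan says.** The first paragraph of Statistical methods, which covers all analyses, states that, where adjustment is needed for "baseline characteristics due to differences among the two groups, this will be performed". The next paragraph gives the primary model, in which "Poisson regression with exponentiated coefficients will be used to produce incidence rate ratios", and generalized linear models for EQ-5D-5L, PCS-12 and MCS-12. No covariate is named for any of them.

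For the economic evaluation, the same section says that effects on effectiveness and costs "will be reported both as an unadjusted estimate and as an estimate that controls for meaningful baseline differences".

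Three other statements bear on the point:

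- The primary outcome is the between-group difference in the "number of observed exacerbations defined as an all-cause acute hospitalization from baseline to follow-up" (Primary outcome).
- The quality-of-life outcome is a change "at the individual level from baseline to follow-up at 6 months" (Secondary outcomes).
- Participants will "by a computer-generated list be allocated randomly (1:1) across two treatment arms", and only after they have completed the baseline questionnaires (Randomization).

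**The concern.** The plan lets the observed data decide whether to adjust and for what. With random allocation, any baseline difference is chance by construction. What a covariate contributes is its correlation with the outcome, and that contribution exists whether or not the arms look balanced. A rule keyed to imbalance therefore discards most of the available precision.

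It also leaves the primary estimate open. Need has no threshold and no list of characteristics to inspect, and no estimate takes precedence. Outcome assessment is not blinded (Study design) and register data are extracted after trial completion (Explorative outcomes), so the article does not place the judgement before the outcomes are visible.

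The baseline SF-12v2 and EQ-5D-5L scores are the clearest case. They are completed before randomisation, yet whether they enter the models depends on how the arms happen to look.

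**Working it through.** **1. The plan's own figure.** Sample size gives 85 per group from means of 2 and 1, 90% power and two-sided 5%. The formula n = 2(1.96 + 1.282)² × SD²/1² gives 84.06, so 85, with SD = 2; 85/0.85 = 100 after 15% loss. (With a variance of 2, as worded, it gives 43; that is a separate matter.) The calculation uses no covariates, so this point does not overturn the sample size.

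**2. Quality of life as change.** Let ρ be the baseline/follow-up correlation, with equal SDs. The documents give no ρ; 0.5–0.7 is assumed. Per participant, in units of the score variance, a change score has variance 2(1 − ρ) and a baseline-adjusted analysis has 1 − ρ². Their ratio is (1 + ρ)/2.

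| ρ | Adjusted/change variance | Reduction |
|---|---|---|
| 0.5 | 0.75 | 25% |
| 0.6 | 0.80 | 20% |
| 0.7 | 0.85 | 15% |

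**3. QALYs.** Linear interpolation over half a year makes the QALY 0.25(U₀ + U₆) for a participant alive throughout. With no treatment effect, a chance baseline difference d is expected to shift the unadjusted QALY difference by 0.25(1 + ρ)d. Assume a utility SD of 0.15–0.25 (not in the documents). With 85 per arm, one standard error of d is SD × √(2/85) = 0.023–0.038. The shift is then 0.25 × 1.5 × 0.023 = 0.009 up to 0.25 × 1.7 × 0.038 = 0.016 QALY.

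**4. Error rate if the result is chosen.** For two standard normal statistics with correlation r, the probability that at least one exceeds 1.96 in absolute value is:

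| r | Error |
|---|---|
| 0.7 | 8.3% |
| 0.8 | 7.8% |
| 0.9 | 7.0% |

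This assumes that the more favourable result is always reported.

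**5. Primary model, by simulation.** Settings: 85 per arm, control mean 2, control variance about 3.7–4.3, three baseline covariates of assumed weak to strong effect, Poisson regression with robust standard errors, 2,500 runs per scenario.

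| Strategy | SE of log rate ratio, no effect | Power at rate ratio 0.7 | Type I error |
|---|---|---|---|
| Unadjusted | 0.150–0.157 | 57–63% | 4.7–5.8% |
| Adjust only where imbalance p < 0.05 | 0.140–0.154 | 58–65% | 4.2–5.3% |
| Prespecified adjustment | 0.110–0.148 | 63–85% | 5.2–5.5% |
| Better of unadjusted and fully adjusted | – | – | 7.2–9.0% |

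The imbalance-triggered rule recovers little of the gain but does not inflate the error. At the protocol's assumed ratio of 0.5, power is about 98–99% unadjusted and above 99% adjusted, so the gain matters mainly if the true effect is smaller. With plain model-based Poisson standard errors, the reported SE is about 0.11 with or without adjustment, which is too small for the unadjusted analysis (type I error 15–18%). The gain is visible only when standard errors allow for overdispersion.

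**The case against.** The strongest reply is that a covariate list is ordinarily left to the analysis plan, which is not shown, and that the sentence says adjustment will be made where needed, not that the analyst may choose. The first half stands for the list but not for the trigger: the article states an imbalance-driven rule, and a later plan would have to override it. The second half stands in part, which bears on three stronger readings.

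- **The plan licenses picking the better of two primary results.** It does not say so. The 7–8% is a worst case that arises only because need is undefined. Applied mechanically, the rule kept its error rate.
- **Chance utility differences go unchecked into the ICER.** The economic section promises both estimates, so an adjusted result would be shown. What remains is that the covariates are those showing "an estimate that controls for meaningful baseline differences", with meaningful undefined and no base case named.
- **Randomisation is unstratified, which worsens the problem.** A condensed article's silence on stratification does not show this.

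A larger precision gain, 25–49% from 1 − ρ², applies against raw follow-up scores. The stated outcome is change, so 15–25% is the relevant range. The generalized linear models are also not said to exclude the baseline score; the article simply does not commit to including it.

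Finally, nothing in the documents shows how strongly earlier admissions predict later ones, so the gain in the primary model cannot be fixed from them.

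**Conclusion.** The point holds and should be corrected, though it does not invalidate the trial. A stated rule makes adjustment depend on observed differences in the primary and quality-of-life models, and a similar criterion selects covariates in the economic models. Neither the primary rate ratio nor the ICER base case is identified as adjusted or unadjusted.

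The firmest loss is in quality of life and QALYs: the baseline scores are already collected, and baseline utility is part of the QALY itself. The 15–25% variance reduction rests on the assumed correlation and equal SDs. For the primary outcome the direction is clear, but the size depends on covariate strength and on standard errors that allow for overdispersion. The error inflation is an upper scenario, not an expected consequence.

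**What to change.** Replace the conditional sentence with covariates fixed in advance and used regardless of imbalance:

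- **EQ-5D-5L, PCS-12 and MCS-12 models:** the baseline value of the same score.
- **QALY model:** baseline EQ-5D-5L utility, with this adjusted estimate as the ICER base case.
- **Primary Poisson model:** a prespecified prognostic covariate, for example the count of acute hospitalisations in a fixed period before baseline, with standard errors that allow for overdispersion.

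Name the adjusted estimate as primary throughout and report the unadjusted one as a sensitivity analysis. Settle this before the register outcomes are linked to allocation.

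Cost: the questionnaire covariates need no new data. The hospitalisation count needs a modest look-back, because the planned extract is described only from baseline to 6 months. Study design requires Regional Ethical Committee approval before any protocol modification, so the wording change must go through that step.

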### Sample size

The sample size calculation is based on the primary outcome. It is assumed that the control group experience an average of two exacerbations, and the intervention group experienced one exacerbation during the trial period from baseline to the 6-months follow-up. With a power of 90%, a variance of two exacerbations for both groups, a two-sided significance level of 0.05, the required sample size is estimated to be at least 85 participants in each group [62]. Based on experience from the original large-scale trial, TeleCare North [34], a loss to follow-up of 15% in each group is expected. Therefore, the total required sample size in each arm is the estimated to be approximately 100 participants.

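### The primary analysis is named as Poisson regression, but the sample-size figures assume one common spread for means of 2 and 1, which cannot be Poisson in both arms

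*Protocol article*

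**What the plan says.** The primary outcome (Primary outcome section) compares the arms on "the number of observed exacerbations defined as an all-cause acute hospitalization from baseline to follow-up", a count per participant over six months. The Statistical methods section gives the analysis in one sentence: "To assess the primary outcome, Poisson regression with exponentiated coefficients will be used to produce incidence rate ratios". The article says nothing about a dispersion parameter, robust standard errors or a negative binomial model.

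The Sample size section assumes that "the control group experience an average of two exacerbations, and the intervention group experienced one exacerbation" over the trial period. It adds "a variance of two exacerbations for both groups", 90% power and "a two-sided significance level of 0.05". From these it derives at least 85 participants per group, raised to about 100 for an expected 15% loss.

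**The concern.** A Poisson model fixes the variance of each count at its mean. With means of 2 and 1, the variances would have to be 2 and 1. The sample-size section gives both arms the same spread, so at least one arm departs from the model named for the analysis, and it departs towards excess variance.

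If standard errors come from the Poisson likelihood and the counts vary as planned, the standard error of the log rate ratio is too small. The p-value and the confidence interval for the trial's single primary comparison would then not have their nominal 5% and 95% properties. The rate ratio estimate itself is not affected.

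**Working it through.** **Inputs (Sample size section):** means 2 and 1, spread of two in both arms, 90% power, two-sided 0.05, 85 per arm, 15% loss.

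**1. Reproducing the stated sample size.** For a difference in means, n per arm = 2 × variance × (1.960 + 1.282)² / difference², and (1.960 + 1.282)² ≈ 10.51.
- SD 2 (variance 4): 2 × 4 × 10.51 / 1 ≈ 84.1, so 85. This matches. Then 85 / 0.85 = 100, which also matches.
- Literal variance 2: 2 × 2 × 10.51 / 1 ≈ 42.0, so 43. This does not match.
- For comparison, a Poisson rate-ratio calculation: 10.51 × (1/2 + 1/1) / (ln 2)² ≈ 32.8, so 33. This does not match.

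The figure of 85 therefore rests on a two-means formula with variance 4. Both readings are carried forward.

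**2. Variance-to-mean ratio.**
- Variance 4: 4/2 = 2 in control, 4/1 = 4 in intervention.
- Variance 2: 2/2 = 1 in control, 2/1 = 2 in intervention.

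**3. Standard error of the log rate ratio at 85 per arm, planned 2 versus 1.**
- Model-based Poisson: √[(1/2 + 1/1)/85] = 0.133.
- Allowing for variance 4: √[(4/2² + 4/1²)/85] = √(5/85) = 0.243, which is 1.83 times larger.
- Allowing for variance 2: √[(2/2² + 2/1²)/85] = √(2.5/85) = 0.171, which is 1.29 times larger.

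Around a rate ratio of 0.50, the 95% interval is 0.39 to 0.65 under model-based Poisson, 0.31 to 0.80 under variance 4 and 0.36 to 0.70 under variance 2.

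**4. Coverage of the nominal 95% Poisson interval under 2 versus 1:** 2Φ(1.96 / SE ratio) − 1.
- Variance 4: 2Φ(1.96/1.83) − 1 ≈ 72% (simulated 73%).
- Variance 2: 2Φ(1.96/1.29) − 1 ≈ 87% (simulated 87%).

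**5. Two-sided type I error of the model-based Poisson test:** 2[1 − Φ(1.96/√(variance/mean))], with the planning variance assumed to hold under no effect.

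| No-effect mean | Variance 4 | Variance 2 |
|---|---|---|
| 2 (planned control mean) | 16.6% | 5.0% |
| 1.5 (assumption) | 23.0% | 9.0% |
| 1 (assumption) | 32.7% | 16.6% |

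Simulation (20,000 trials per scenario, 85 per arm; negative binomial counts, or Poisson where variance equals mean) gave 16.4%, 22.7% and 31.8% for variance 4, and 4.9%, 8.7% and 16.3% for variance 2. A robust-variance test on the same data rejected 5.0% to 5.6% of the time throughout.

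**6. Power of a robust rate-ratio test at 85 per arm:** Φ(ln 2 / SE − 1.96).
- Variance 4: Φ(0.693/0.243 − 1.96) ≈ 82% (simulated 85%). For 90%: 10.51 × 5 / (ln 2)² ≈ 109.3, so 110 per arm.
- Variance 2: about 98%.

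**The case against.** The strongest reply is that the article names Poisson regression but not its variance estimator. Poisson regression with sandwich errors would satisfy the same sentence, and an analysis plan that is not shown may say so. That stands as a condition: every error rate and coverage figure above applies only if model-based errors are used. It does not remove the mismatch, because the named model and the planning figures disagree within the article itself.

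A second reply is that a common spread in a two-means formula is a working input, not a claim about how the counts are distributed. This is fair. The article gives no observed dispersion and does not say that admissions cluster in a few patients. It says only that exacerbations become more frequent with severity (Background) and that any COPD stage is admitted (Inclusion criteria). That makes unequal rates between patients plausible but does not quantify them.

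A reader might go further and infer that the primary test is grossly anti-conservative whichever way the figures are read. The documents do not support this. On the printed variance of 2, the control arm is exactly Poisson and type I error at the planned control mean is 5%. The 23% and 33% figures need a no-effect mean below 2 with variance held at 4, and the article states neither. Nor does it follow that a chance difference would probably be reported as a benefit. A two-sided 17% means about 8% false reductions, since half fall in each direction.

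**Conclusion.** The point holds as an internal conflict between the analysis model and the planning assumptions. One spread for means of 2 and 1 cannot be Poisson in both arms on either reading.

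The size depends on which reading is right. With variance 4, the only reading that gives 85 per arm, model-based errors produce about 17% type I error at the planned control mean and about 72% coverage under the planned effect. With the printed variance of 2, the figures are 5% and 87%. So coverage under the planned effect falls short on both readings, while type I error at a mean of 2 is inflated only on the variance-4 reading.

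These results assume model-based errors, 85 analysed per arm, and a planning variance that also applies under no effect.

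**What to change.** Replace the sentence on the primary analysis with one stating that the number of acute hospitalisations per participant is analysed on the log scale, with log follow-up time as offset, by Poisson regression with robust (sandwich) variance or by negative binomial regression. One of the two should be chosen in advance, and model-based Poisson kept only as a sensitivity analysis. The sandwich option does not need a common dispersion parameter. A standard negative binomial model does, and the planning figures do not share one: with variance 4, (4 − 2)/2² = 0.5 in control and (4 − 1)/1² = 3 in intervention.

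In the Sample size section, state whether two is a variance or a standard deviation, and restate power on the rate-ratio scale.

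No new data are needed. Intervals will be wider and p-values larger when counts are overdispersed. If the standard deviation is 2, the robust test has about 82% power at 85 per arm, and 90% would need about 110 analysed per arm, more than the 100 planned for enrolment. If the variance really is 2, power at 85 remains about 98%.
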